### Assessments of underlying statistical assumptions

2.14

We will systematically assess underlying statistical assumptions for all statistical analyses.^23^, ^24^ In short, we will test for major interactions between the three intervention variables for all primary and secondary regression analyses. We will only consider that there is evidence of an interaction if the interaction is statistically significant (*p* < .01) and if the interaction shows a clinically important effect (based on the anticipated intervention effect used in the sample size, that is, an absolute risk reduction of 5.6%). If it is concluded that the interaction is significant both statistically and clinically, we will reconsider whether the three comparisons should be presented in three separate main articles.^23^, ^24^

#### Assessments of underlying statistical assumptions for dichotomous outcomes

2.14.1

We will assess if the deviance divided by the degrees of freedom is significantly larger than 1 to assess for relevant overdispersion. Overdispersion is the presence of greater variability (statistical dispersion) than expected in a data set based on a given statistical model. Relevant overdispersion will be handled using a maximum likelihood estimate of the dispersion parameter. To avoid analytical problems with few events or problems with all participants dying at a given site, we have only included sites planning to randomize at least 30 participants. We will consider pooling data from smaller sites if the number of participants is too low.^24^

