### Sample size and power estimations

2.10

Based on the results of the TTM trial, TTM2 trial, and information from the International Cardiac Arrest Registry (INTCAR),^9^ we estimate that within 6 months after randomization, approximately 60% of the participants will die. We hypothesize that 6 months after randomization, 54.4% of the participants will die in the intervention groups, corresponding to a relative risk reduction of 9% (relative risk, RR = 0.91). With an acceptable risk of type‐1 error of 5% and an acceptable risk of type‐2 error of 10% (power of 90%), a total of 3278 participants (1639 in each pairwise comparison) would be required.

We plan to investigate the possible effects of adjustment for site and possible interactions between interventions using simulations.^10^ Preliminary simulations suggest that if there are interactions between the trial interventions on outcomes, it would be necessary to increase the sample size. The STEPCARE trial is being conducted with the assumption that there will be no such interactions between the trial interventions on outcomes. However, to accommodate the possibility of minor interactions, an increase in the sample size (5%) has been chosen to account for this. The combined effect of withdrawn consent and missing data on the primary outcome in the TTM2 trial resulted in a sample size reduction of approximately 2%. We assume a similar result in the current trial (1.8%). Considering the above‐mentioned factors, we will increase the sample size by 6.8% and recruit a total of 3500 participants.

We estimated the statistical power of all secondary outcomes.^11^ With an estimated sample size of 3500 participants in total, the functional outcome measure (dichotomized mRS) has a power of 98% to detect a relative risk of 0.90 for a poor functional outcome (mRS 4–6) in the experimental group, with 65% of cases in the control group experiencing a poor functional outcome.

For the predefined serious adverse events, we performed simulations to assess the incidences for the three serious adverse event outcomes. We had estimated incidences for arrhythmia, sepsis, and bleeding, but not for unplanned extubation, reintubation, and venous thromboembolism.^12^, ^13^ We also considered aggregate data from previous meta‐analyses and trials, and these numbers roughly corresponded to the simulations:^3^, ^4^, ^14^, ^15^, ^16^

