### General analysis principles

2.11

We will conduct all analyses according to the intention‐to‐treat principle (ITT), that is, all randomized participants with available data will be included in all analyses.

We will assess if the statistical and clinical significance thresholds are crossed (Bayes factor calculations will be reported in supplementary material).^17^ Assessment of clinical significance will be based on the anticipated intervention effects used in the sample size and power estimations.^17^ Our primary conclusion will be based on the primary outcome, so all tests of statistical significance (including subgroup analyses) will be two‐sided with a threshold of 5%.^17^ No conclusions will be drawn based on secondary outcomes.

It is generally acknowledged that regression analyses ought to be adjusted for the stratification variables used in the randomization.^18^, ^19^, ^20^ Hence, when analyzing each of the three trials, we will adjust all analyses for ‘site’ and the allocated intervention in the two other trials (e.g., the SED‐CARE outcomes will be adjusted for ‘site’ and the allocated TEMP‐CARE and MAP‐CARE interventions). We will assess whether there are significant interactions between trial interventions (for details, see Section 2.14).

We will perform the following subgroup analyses:Age (higher or lower than the median)Sex (male/female)Cardiopulmonary resuscitation by bystander (yes/no)Initial rhythm (shockable vs. non‐shockable)Time to ROSC (higher or lower than the median)Circulatory status on admission (presence or absence of circulatory shock diagnosed by the treating physician)Baseline risk of poor neurologic outcome (Miracle2‐score: low risk (0–2), medium (3–5), and high (6–10).^21^)Presumed cause of arrest at randomization (cardiac vs. others)Chronic hypertension as a comorbidity

We plan to reanalyze all three trials using Bayesian statistics. Separate statistical analysis plans will be published.

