#### Outcomes

2.12.1

We will analyze the primary outcome as a binary variable (alive or dead). We will analyze the secondary outcomes as follows: (I) We will evaluate the functional outcome by dichotomizing the modified Rankin scale (0–3 vs. 4–6), or if this is missing, dependent versus independent in basic activities of daily life (moving indoors, eating, dressing, personal hygiene). (II) We will analyze serious adverse events as a binary variable (one or more versus no serious adverse event). Additionally, we will present each specific serious adverse event separately by risk ratios and 95% confidence intervals. (III) We will analyze HRQoL by EQ‐VAS scale as a continuous variable (0–100).

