#### Analysis of dichotomous data

2.12.2

We will present dichotomized outcomes as proportions of participants in each group with the event, as well as relative risks with 95% confidence intervals. We will analyze dichotomous outcomes using mixed effects generalized linear models using a log‐link function with ‘site’ as a random intercept using an exchangeable covariance matrix, and we will include the allocated intervention in the two other trials as fixed effects. If the analysis does not converge, we will use mixed effects logistic regression to analyze dichotomized data and relative risks will be obtained using either G computation in R (R Core Team, Vienna, Austria) or the NLCOM command in Stata 18 (StataCorp, College Station, TX, USA).

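### For individual 0/1 outcomes the deviance/df overdispersion check carries no information: under a binomial model it is positive almost surely for the main binary outcomes, and the stated remedy is undefined for such data

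*SAP article*

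**What the plan says.** Section 2.14.1 of the SAP article sets a trigger and a response for all dichotomous outcomes. The trigger is: "We will assess if the deviance divided by the degrees of freedom is significantly larger than 1 to assess for relevant overdispersion". The response is: "Relevant overdispersion will be handled using a maximum likelihood estimate of the dispersion parameter".

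The outcomes concerned are individual binary values. Section 2.12.1 says: "We will analyze the primary outcome as a binary variable (alive or dead"). Poor functional outcome and the serious adverse event composite are also coded yes/no per participant, and each single adverse event gets its own risk ratio and 95% confidence interval.

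The model is in section 2.12.2: "We will analyze dichotomous outcomes using mixed effects generalized linear models using a log"-link function, with site as a random intercept and the other two allocations as fixed effects. The distribution family is not named. The fallback is: "If the analysis does not converge, we will use mixed effects logistic regression to analyze dichotomized data". That model is Bernoulli.

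Nothing in the article says that data are grouped before the check, that a Pearson statistic is used, or how the dispersion estimate enters the standard errors.

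**The concern.** Overdispersion means more variance than the model's mean-variance relation allows. It can be seen in grouped counts (deaths out of n at a site). It cannot be seen in a single 0/1 value, whose variance is p(1-p) whatever the mechanism. Deviance/df on such data therefore does not compare observed with expected variation. Its size is set by the event rate, and at rates near 50 to 65% it lies well above 1 even when the model is exactly right.

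The rule governs the primary outcome in all three comparisons, and the primary conclusions rest on that outcome. A trigger that fires on correct data leads to a remedy that has no definite meaning for these data. Two competent analysts could respond differently and reach different confidence intervals. Section 2.15 has two statisticians analyse independently, with the steering group choosing between discrepant results, so the ambiguity could reach the primary result. The plan's stated purpose is to avoid such data-driven choices.

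**Working it through.** **Inputs from the SAP article.** Control mortality (section 2.10): "approximately 60% of the participants will die". Intervention mortality 54.4% (RR 0.91), two-sided 5%, power 90%, 3278 participants before inflation, 3500 to be recruited. Control-group rates: poor functional outcome 65% (RR 0.90); serious adverse event composites 61% in SED-CARE (RR 0.91), 63% in TEMP-CARE (RR 0.91) and 57% in MAP-CARE (RR 0.90).

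**The plan's own figure.** Two proportions, pooled variance under the null, no continuity correction, mean p = 0.572:

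n per arm = [1.960 x sqrt(2 x 0.572 x 0.428) + 1.282 x sqrt(0.6 x 0.4 + 0.544 x 0.456)]^2 / 0.056^2 = 1639, total 3278. This matches.

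**Expected deviance/df with no overdispersion.** For ungrouped 0/1 data the saturated log-likelihood is zero, so the expected deviance per participant is

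d(p) = -2[p ln p + (1-p) ln(1-p)].

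d(0.60) = 1.346 and d(0.544) = 1.379; the mean over two equal arms is 1.362. The same formula for the other main outcomes:

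| Outcome | Control / intervention rate | Expected deviance/df | Square root |
|---|---|---|---|
| Mortality | 0.60 / 0.544 | 1.362 | 1.167 |
| Poor functional outcome | 0.65 / 0.585 | 1.326 | 1.152 |
| SED-CARE composite | 0.61 / 0.555 | 1.356 | 1.164 |
| TEMP-CARE composite | 0.63 / 0.573 | 1.341 | 1.158 |
| MAP-CARE composite | 0.57 / 0.513 | 1.376 | 1.173 |

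**Limit for a significant result.** With 3500 participants and four fixed parameters, df = 3496. The upper 5% point of chi-square divided by df is 1.040. All five expected values are far above it.

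**Simulation.** 3500 participants in an assumed 70 sites of 50, with an assumed site SD on the logit scale of 0, 0.3 or 0.5 and 300 runs each:

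- Individual-level log-binomial model without site: deviance/df averaged 1.36 and was significant in 100% of runs (minimum 1.33). Pearson/df on the same data averaged 1.00 and was significant in none.
- Logistic model with site fixed effects (40 runs per setting): deviance/df 1.37, 1.35 and 1.32. Adjusting for site does not bring the ratio near 1.
- Data grouped by site and arm, site not in the model: with no site effect, deviance/df was 1.03 and significant in 5% of runs, as a valid test should be. With site SD 0.3 and 0.5 it was 1.57 and 2.42 and significant in 98% and 100%, correctly showing between-site variation.

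**Where it does not fire.** d(p) = 1 at p of about 0.20; d(0.10) = 0.65 and d(0.05) = 0.40. Under a Poisson family with log link the ratio is about -2p ln p = 0.64 at p = 0.572. Here too the ratio follows from the event rate and says nothing about extra variation.

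**What the remedy could do.** A 0/1 distribution is fixed by its mean, so a separate dispersion parameter is not identifiable by maximum likelihood. Two substitutes bracket the effect:

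- Pearson-based estimate of about 1.00: no change.
- Standard errors scaled by sqrt(1.362) = 1.167: at 1639 per arm, SE = sqrt[(0.24 + 0.2481)/1639] = 0.01726. Power before scaling is Phi(0.056/0.01726 - 1.96) = 0.90; after scaling, Phi(0.056/(0.01726 x 1.167) - 1.96) = 0.79. At 1750 per arm it goes from 0.92 to 0.82. The two-sided type I error becomes 2 x [1 - Phi(1.96 x 1.167)] = 0.022.

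**The case against.** A reader might infer that the plan, followed as written, widens every binary-outcome confidence interval by 17% and forfeits the stated 90% power. The document does not support that, for three reasons:

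- It never says that standard errors are multiplied by sqrt(deviance/df). The 17%, the 79% power and the 2.2% type I error belong to one possible implementation of an undefined remedy.
- Not every binary outcome is affected. Single adverse events with a risk under about 20% would not trigger the check, and the five main outcomes give 15 to 17%, not one uniform figure.
- The first-line model names no family and section 2.14.1 names no level of aggregation. Under a Poisson family, or on suitably grouped data, the check would not fire spuriously. Only the logistic fallback fixes the Bernoulli case.

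It can also be said that the word relevant leaves room for judgement, that the random intercept already covers site variation, and that an analyst who finds the parameter cannot be fitted would probably drop the step. Even deviance scaling would err on the conservative side and leave the point estimate unchanged.

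All of this limits the size and severity of the point. It does not rescue the check, which is uninformative for individual 0/1 data under either family. The threshold for relevant is not given, and dropping a pre-specified step after seeing its result is the kind of unplanned decision that the SAP exists to prevent. Nor is this detail left out by a condensed article: the test and the response are both stated, and they do not suit the outcomes as defined.

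**Conclusion.** Wrong as written; it should be fixed, but it is not critical. On individual-level data under a binomial family, the check is positive almost surely for mortality, poor functional outcome and the three composites, with no overdispersion present. The effect of the remedy is not determined by the plan. It ranges from none to a widening of about 15 to 17% for the main outcomes, which would cost the primary outcome about 11 percentage points of power at 3278 participants.

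The near-certain trigger assumes individual-level binomial analysis and event rates near those planned. The expected ratios follow from those rates alone; the number, size and variability of sites are assumptions and affect only the simulated figures.

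**What to change.** Remove the deviance/df check and the dispersion correction for individual-level binary outcomes in section 2.14.1. State that the variance of a binary outcome is fixed by its mean and that between-site variation is handled by the site random intercept.

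If a check is still wanted, do one of the following:

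- Run it on data grouped by site and arm, and say whether site is in the model being checked. Without a site term, a positive result shows only the between-site variation that the random intercept already covers, so it should not trigger a further correction.
- Report site-clustered robust standard errors as a sensitivity analysis.

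Naming the distribution family of the log-link model in section 2.12.2 would remove the remaining ambiguity. The cost is a few sentences of SAP wording, with no change to design, data collection or sample size. It should be settled before the outcome data are analysed.

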#### Assessments of underlying statistical assumptions for linear regression

2.14.2

We will visually inspect quantile–quantile plots of the residuals to assess if the residuals are normally distributed and use residuals plotted against covariates and fitted values to assess for homogeneity of variances.^25^, ^26^ If the plots show deviations from the model assumptions, we will consider transforming the outcome, for example, using log transformation or square root and/or using robust standard errors.^24^, ^25^, ^26^

### Statistical reports

2.15

Blinded data on all outcomes will be analyzed by two independent statisticians.^24^ Two independent statistical reports will be sent to the chief principal investigator and will be shared with the steering group and author group, and if there are discrepancies between the two primary statistical reports, then possible reasons for those will be identified and the steering group will decide which is the most correct result. We will prepare one final statistical report and publish all three statistical reports as supplementary material.^24^

## DISCUSSION

3

The aim of this predefined statistical analysis plan is to minimize the risk of biased data‐driven analyses. This statistical analysis plan describes the analyses for the three STEPCARE trials: SED‐CARE, TEMP‐CARE, and MAP‐CARE in detail.

This statistical analysis plan has several strengths. The methodology is predefined and detailed to avoid data‐driven analyses and risks of outcome reporting bias. All primary and secondary outcomes are patient‐centered, and our primary conclusions will be based on the primary outcome to limit problems with multiplicity.^17^ We will analyze data according to the intention‐to‐treat principle and, if necessary, use multiple imputation and best‐worst/worst‐best case scenarios to assess the potential impact of the missing data on the results.^22^ Furthermore, we plan to systematically assess whether underlying statistical assumptions are fulfilled for all statistical analyses.

This statistical analysis plan also has limitations. Our primary conclusions will be based on the main outcome, while we will also evaluate secondary outcomes, exploratory outcomes, and subgroup analyses. We have not adjusted our significance thresholds for all comparisons, acknowledging that this approach increases the risk of type I errors. Additionally, the anticipated intervention effects, which informed our sample size and power calculations for the secondary outcomes, are based on a pragmatically applied identical intervention effect across all three trials using clinical judgment and results from earlier similar trials. This anticipated effect is deemed both realistic and of significant value to patients. When drawing final conclusions, we will consider the elevated risk of type I errors and uncertainties surrounding the anticipated intervention effects.

## CONCLUSION

4

Here we describe the statistical analyses for the STEPCARE trial in detail. The aim of this predefined statistical analysis plan is to minimize the risk of analysis bias.

## Data Availability

Not applicable. All available data are included in this manuscript.
